### 7.1.6 Immunization Phase Day 14 ( 2 days; Second Treatment):

- Vital signs will be taken and recorded
- An interval medical history will be performed to ensure that each subject continues to meet all inclusion and no exclusion criteria.
- A urine specimen will be collected from each female subject and tested in the clinic for evidence of pregnancy. No test article will be administered until a negative result is obtained and documented.
- A directed examination of the ears, cervical lymph nodes, and nasopharynx will be performed, the results of which will be recorded using the worksheet provided as Appendix C.
- Each subject will be interviewed regarding the presence of baseline upper respiratory complaints and / or symptoms of systemic illness prior to dosing, using a “Memory Aid” format consistent with that presented in Appendix D.
- Volunteers with any grade 2 physical findings or grade 2 symptoms among their baseline Memory Aid observations will not be given a test article dose.
- These subjects may return to the clinic up to Immunization Phase Day 21 and, if symptoms or findings have resolved, receive the second test article dose. Up to Immunization Phase Day 16, this will not be recorded as a protocol deviation; from Immunization Phase Days 17 to 21 a deviation will be recorded but the dose will be given. Such subjects will complete all protocol-mandated follow-up per schedule and *will* be eligible for challenge.
- If grade 2 symptoms or findings persist beyond Immunization Phase Day 21, the second dose will be withheld. Such subjects will not be eligible for challenge, but will complete all other protocol-mandated follow-up.

 Test article will be administered intranasally as described in section 6.5.

 Subjects will be observed for thirty (30) minutes after dosing. At the end of this interval, each subject will have an oral temperature measured and recorded and complete a questionnaire eliciting immediate post-immunization symptoms (present at the time of observation or in the preceding 30 minutes). Each will be graded as: none, mild (just noticeable), moderate (unpleasant/uncomfortable, but not incapacitating), or severe (preventing resumption of normal activities). The questionnaire is provided as Appendix E.

 Each subject will be provided with a Memory Aid (Appendix D) and a new digital thermometer (if needed) and instructed to take his/her temperature and complete a Memory Aid page each evening from Immunization Phase Days 14 to 20. Subjects will be instructed to notify the clinic (Retroscreen) should they experience grade 2 or greater symptoms, and to return as instructed for physician evaluation.

 Subjects will be instructed to return on Immunization Phase Day 21, with their Memory Aid.

### 7.1.7 Immunization Phase Days 14 to 20 (0 – 6 days after the Second Treatment)

- Subjects will maintain their Memory Aids and measure evening temperatures daily.
- Subjects will report any grade 2 or greater symptoms, or fever (oral temperature ≥ 37.9º C) to study site personnel, who will arrange for a physician evaluation.
- Physician evaluations will be performed as needed, and recorded in a uniform manner utilizing the worksheet provided as Appendix C.

### 7.1.8 Immunization Phase Day 21 (± 2 days; Follow-up Visit Two):

 Vital signs will be taken and recorded.

 Each subject’s Memory Aid will be reviewed, collected, and the data abstracted and recorded. Subjects who have lost their Memory Aids will be provided with new documents, which will be completed from memory with the assistance of the interviewer. Such data will be clearly annotated as RETROSPECTIVE.

 Subjects will be queried regarding the occurrence of adverse events not specified in the Memory Aid, and any new concomitant medications taken, and the results recorded.

 A brief, directed examination of the ears, cervical lymph nodes, and naso-pharynx will be performed to detect objective signs of vaccine-induced reactogenicity. The examiner will complete the brief exam worksheet provided as Appendix C.

 Subjects will be given an appointment to return to the clinic on Immunization Phase Day 28  3.

### 7.1.9 Immunization Phase Day 28 ( 3 days; Follow-up Visit Three):

- Subjects will be queried regarding the occurrence of adverse events and any new concomitant medications taken, and the results recorded.
- A physical examination will be performed *if required* to evaluate any complaints, and new abnormalities will be captured as adverse events.

 A nasal wash specimen for specific antibody assay will be obtained from each subject (see section 7.2).

 Approximately 40 mL of blood will be drawn from each subject for HAI antibodies, *in vitro* cytokine stimulation studies, and clinical laboratory tests (see section 7.2).

- Each subject will provide a urine specimen for determination of blood, glucose, and protein.

### 7.1.10 Challenge Phase Day 0 (39  3 days after First Treatment; Admission to Quarantine):

 All subjects will be admitted to the quarantine unit.

- An interval medical history will be performed to ensure that each subject continues to meet all inclusion and no exclusion criteria (excepting influenza vaccine and serum HAI criteria, which will have become irrelevant due to the immunization component of this protocol).
- Subjects will be queried regarding the occurrence of adverse events and changes in concomitant medications, and the results recorded.
- Subjects will complete an Influenza Symptom Diary Card (see Appendix F), and will be interviewed by a physician re: potential symptoms of influenza or upper respiratory infection.
- A complete physical examination, including vital signs with oral temperature, will be performed and recorded.
- An ECG will be performed.

 A nasal wash specimen for specific antibody assay will be obtained from each subject (see section 7.2).

 Approximately 15 mL of blood will be drawn from each subject for specific HAI serologies (see section 7.2).

7.1.11 Challenge Phase Day 1:

 Subjects will have oral temperature measured and recorded four times a day.

- Subjects will complete an Influenza Symptom Diary Card (see Appendix F), and will be interviewed by a physician, approximately every 12 hours.
- Subjects will be queried regarding occurrence of AEs not specified in the Influenza Symptom Diary Card, and these will be recorded.
- A directed physical examination using the Challenge Physical Examination Worksheet (see Appendix G) will be performed and recorded in the evening.
- Subjects will be instructed in, and begin, collection of used tissues for 24 hour-counts and weights.
- Any subject with grade 2 findings or complaints and/or an oral temperature ≥ 37.9 º C (confirmed by repetition at an interval of not less than 20 minutes) will be immediately segregated from the remaining subjects and discharged if any suspicion of an **intercurrent** respiratory infection exists. The examining physician will provide medical referral for outpatient care if deemed necessary. The cause of such discharge will be recorded as an adverse event. The subject will be instructed to return for the day 60 outpatient visit.

### 7.1.12 Challenge Phase Day 2, Morning (Day of Challenge):

- Subjects will complete a morning Influenza Symptom Diary Card (see Appendix F).
- Subjects will be queried regarding occurrence of AEs not specified in the Influenza Symptom Diary Card, and these will be recorded.
- A urine specimen will be collected from each female subject and tested in the clinic for evidence of pregnancy. No challenge virus will be administered until a negative result is obtained and documented.
- Any subject with grade 2 complaints and/or an oral temperature ≥ 37.9 º C (confirmed by repetition at an interval of not less than 20 minutes and not more than 60 minutes) will be immediately segregated from the remaining subjects and discharged if any suspicion of an intercurrent respiratory infection exists. The examining physician will provide medical referral for outpatient care if deemed necessary. The cause of such discharge will be recorded as an adverse event. The subject will be instructed to return for the day 60 outpatient visit.
- Each subject remaining eligible will provide a throat swab for detection and / or quantitation of influenza virus **using culture, antigen detection and / or molecular biology techniques** (see section 7.2).

 Each subject remaining eligible will be challenged with A/Panama/2007/99 delivered nasally by dropper.

7.1.13 Challenge Phase Day 2 Afternoon to Challenge Phase Day 9 Morning.:

- Subjects will complete an Influenza Symptom Diary Card (see Appendix F), and will be interviewed by a **member of the medical team**, approximately every 12 hours.
- Subjects will have an oral temperature measured and recorded four times a day.
- Subjects will be queried regarding occurrence of AEs not specified in the Influenza Symptom Diary Card, and these will be recorded.
- A directed physical examination using the Challenge Physical Examination Worksheet (see Appendix G) will be performed and recorded.
- Subjects will continue 24-hour tissue collections for counts and weights.
- Every morning (beginning on Challenge Phase Day 3), *after physical examinations are completed*, a nasal wash and a throat swab will be obtained **from each subject for detection and / or quantitation of influenza virus using culture, antigen detection and/or molecular biology techniques** (see section 7.2).
- Symptomatic treatment with paracetamol (1000 mg orally no more than q.i.d.) will not be offered, but may be given upon subject request *if and only if*:
  - The subject has an oral temperature ≥ 38.5º C (confirmed by a second measurement separated by not less than 20 minutes or more than 60 minutes, or
  - The subject has a confirmed oral temperature of ≥ 37.9º C, and at least one concurrent symptom of grade 2 or greater severity, or
  - The subject has two or more concurrent symptoms of grade 2 or greater severity.
- **Specific treatment with oseltamivir 75 mg orally administered twice daily may be begun before Challenge Phase Day 8 *if and only if*:**
  - **The subject has a confirmed oral temperature ≥ 39.0º C, or**
  - **The subject has a confirmed oral temperature of ≥ 38.5º C, and at least two (2) concurrent symptoms of grade 2 or greater severity, or**
  - **The subject has three (3) or more concurrent symptoms of grade 2 or greater severity or two (2) symptoms of grade 3 severity**
- On the MORNING of Challenge Phase Day 8, all subjects will initiate treatment with oseltamivir (75 mg orally), to be administered twice daily at approximately 12 hour intervals for five (5) days. Subjects who are intolerant of oseltamivir – most commonly manifesting with nausea or other gastrointestinal symptoms which are atypical for influenza – may be treated with amantidine hydrochloride 200 mg orally once a day for three days or until influenza symptoms resolve.
- On either Challenge Phase Day 8 or 9, a complete physical examination, including vital **signs, and** an ECG will be performed and the results recorded.

7.1.14 Challenge Phase Day 9 p.m.:

- Oseltamivir or amantidine treatment will continue as per 7.1.13.
- Subjects will complete an Influenza Symptom Diary Card (see Appendix F), and will be interviewed by a physician.
- Subjects will be queried regarding occurrence of AEs not specified in the Influenza Symptom Diary Card, and these will be recorded.
- Subjects who are afebrile (oral temperature < 37.9º C) and free of influenza-like illness symptoms of grade 2 severity, and have no ominous findings on their Challenge Phase Day 8 or 9 physical examination may be discharged with instructions to return to the clinic for the Challenge Phase Day 20 – 30 outpatient visit. Subjects will be supplied with sufficient oseltamivir or **amantidine** to complete their five-day regimen, and reminded to do so. Any subject who is either febrile (temperature > 37.9º C) or has persistent symptoms of grade 2 or greater (see diary card) will be retained in the facility for 24 hours additional observation and drug treatment unless the Investigator records a clear and compelling medical rationale for allowing discharge. Subjects who continue significantly symptomatic will be referred for appropriate medical care as needed.

7.1.15 Challenge Phase Day 20 – 30 (56 – 72 days after First Treatment; Final Follow-up Visit)

- Subjects will be queried regarding the occurrence of adverse events and any new concomitant medications taken, and the results recorded.
- A complete physical examination, including vital signs, will be performed and recorded.
- An ECG will be repeated if significant new abnormalities were noted prior to discharge from the quarantine facility.
- A nasal wash specimen for specific antibody assay will be obtained from each subject (see section 7.2).
- Subjects will provide a 15 mL sample of blood for HAI antibody testing (see section 7.2).
- This visit marks completion of protocol IDB-13005.

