## 9.3 Illness Definitions and Analysis for Challenge Component:

9.3.1 Fever:

Fever will be defined as any oral temperature 37.9C which is confirmed by a repeat observation at an interval of not less than 20 minutes and not more than 60 minutes. Prior experience has shown that electronic digital thermometers used in climate-controlled environments may not precisely reflect the normal oral temperature range established in the era of mercury bulb instruments used in ambient conditions. Accordingly, an alternative definition of fever, i.e., ≥ 3 standard deviations above the mean of the third temperature observation on **Challenge** Phase Day 1, will be utilized if significantly lower than 37.9º C.

9.3.2 Upper Respiratory Illness:

A subject will be considered to have upper respiratory illness if he or she has any one of the following on two (2) consecutive days, at least one (1) day of which must feature grade 2 severity, or if any of the following attain grade 3 severity once:

- Self-reported symptoms:
  - Rhinorrhea (runny nose), or
  - Nasal congestion (stuffy nose), or
  - Sore throat.
- Physician findings:
  - Nasal discharge
  - Otitis
  - Sinus tenderness
  - Pharyngitis

9.3.3 Lower Respiratory Illness:

A subject will be considered to have upper respiratory illness if he or she has any one of the following on two (2) consecutive days, at least one (1) day of which must attain grade 2 severity, or if any of the following attain grade 3 severity once:

- Self-reported symptoms:
  - Cough, or
- Physician findings:
  - New wheezing, rhonchi, râles, or signs of consolidation

9.3.4 Systemic Illness:

A subject will be considered to have upper respiratory illness if he or she has any one of the following on two (2) consecutive days, at least one (1) day of which must attain grade 2 severity, or if any of the following attain grade 3 severity once:

- Headache
- Myalgia and/or athralgia

9.3.5 Illness (Any):

A subject will be considered to have illness if he/she fulfills the criteria for fever, or upper respiratory illness, or lower respiratory illness, or systemic illness or any combination thereof.

9.3.6 Infection:

A subject will be deemed to be infected if he/she has any one of:

- Influenza virus shedding in nasal wash at any level, or
- Detection of influenza virus in the throat swab by using **culture, antigen detection or** molecular biology techniques, or

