Additional secondary analyses will be based on tissue counts (and weights, if feasible) as a marker of illness severity, and on virus shedding assessed by two methods: peak and a time-weighted average calculated as a trapezoidal-rule AUC. For both peak and AUC, viral shedding is in units of log10 (titer). These continuous data will be compared between cross-over groups by Student’s t-tests and Wilcoxon tests and, in a more flexible analysis, by linear model adjusted for the demographic and clinical covariates cited above.

Finally, the three binary measures of influenza and the two viral load estimates (peak titer and AUC) will be assessed relative to the two immunologic measures, HAI reciprocal titer and nasal secretory IgA. For the binary measures, mean viral load (for each measure) is compared by t-tests between those with and without influenza (for each definition). For the two immunologic measures, the test of association with viral load will be based on Pearson correlations of log-titers.

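### Symptom-only rescue in 7.1.13 can start on one afebrile day, but 9.3.2–9.3.4 need a grade 2 symptom on two days, so treatment can remove the day that defines illness; the shedding AUC also mixes samples on and off antiviral

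*Protocol*

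**What the plan says.** Protocol section 7.1.13 lists the conditions for symptomatic and antiviral treatment after challenge. Paracetamol "will not be offered, but may be given upon subject request". Two of its three criteria need a confirmed temperature of at least 37.9 ºC. The third does not: "The subject has two or more concurrent symptoms of grade 2 or greater severity". Oseltamivir may start before Challenge Phase Day 8 on either of two temperature criteria, or on "three (3) or more concurrent symptoms of grade 2 or greater severity or two (2) symptoms of grade 3 severity". None of the symptom criteria asks how long the symptoms have lasted.

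The illness definitions are stricter on duration. Section 9.3.2 requires "any one of the following on two (2) consecutive days, at least one (1) day of which must feature grade 2 severity", or grade 3 severity once. Sections 9.3.3 and 9.3.4 use the same pattern for cough and chest findings, and for headache and muscle or joint aches. Section 9.3.5 makes Illness (Any) the union of fever and these three categories; treatment is not a component. Section 9.3.7 adds infection to obtain laboratory-confirmed illness.

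For shedding, section 9.3.8.2 specifies "virus shedding assessed by two methods: peak and a time-weighted average calculated as a trapezoidal-rule AUC". Section 7.2.7 takes a nasal wash and throat swab daily from Challenge Phase Day 3 to Day 9. Under 7.1.13 every subject starts oseltamivir on the morning of Day 8.

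**The concern.** The rescue thresholds and the illness thresholds use the same symptom grades on different clocks. A subject with grade 2 headache, aches and sore throat on one day may be treated that day. If treatment clears the symptoms by the next day, the second day never occurs and the subject is scored as not ill. That subject was more symptomatic than one with a single untreated grade 2 symptom followed by a grade 1 day, who counts as ill. Diary grade 2 (Appendix F) is a modest level: bothersome at times, without stopping activities.

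At stake is the count behind Illness (Any), the outcome used for power in 9.3.8.1, and behind laboratory-confirmed illness, which inherits it. With about 25 challenged per group (section 4.1), a few subjects matter. For shedding, samples taken on an antiviral and samples taken off it enter one summary.

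**Working it through.** **1. The plan's own power figure.** Inputs: 28 per group, placebo illness about 50–60% and a 70% reduction (9.3.8.1); two-sided 0.05 (9.0). With p̄ = (p1 + p2)/2,

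power = Φ{ [|p1 − p2| − 1.96·√(2p̄(1 − p̄)/n)] / √[(p1(1 − p1) + p2(1 − p2))/n] }.

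For 50% v 15%: p̄ = 0.325, so (0.350 − 1.96 × 0.1252)/0.1161 = 0.90 and power = 0.816. For 60% v 18% it is 0.919. The stated figure of at least 0.80 is reproduced. There is little reserve. At 25 per group, 50% v 15% gives 0.769. With Fisher's exact test (9.0 says chi-square tests are exact) it is 0.752 at 28 and 0.676 at 25.

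**2. Which rescued subjects escape the illness definition.**
- Temperature criteria: each needs a confirmed reading of at least 37.9 ºC, which is already fever under 9.3.1 and so illness. No gap.
- Two grade 3 symptoms: one listed symptom at grade 3 once is already illness. No gap.
- Two (paracetamol) or three (oseltamivir) concurrent grade 2 symptoms: a gap is possible.

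For the last group, enumerate grades 0–3 for each triggering symptom on the day before, the day of and the day after rescue. A symptom qualifies if it is present (grade 1 or more) on two consecutive days with at least one day at grade 2, or reaches grade 3 once. Requiring grade 2 or more on the rescue day leaves 4 × 2 × 4 = 32 sequences per symptom: 32² = 1,024 patterns for two symptoms and 32³ = 32,768 for three. In each case exactly one pattern is not ill: grades 0, 2, 0 for every triggering symptom. A grade 1 trace on either side makes the subject ill. So does fever, another qualifying symptom or a qualifying physician finding. These counts show the shape of the gap; they are not probabilities.

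**3. Size, as a range.** The share of cases missed is not in the protocol; 0–20% is assumed. True efficacy is 70% and n = 28. Observed rates are p1(1 − f_placebo) and 0.3·p1(1 − f_active); power uses the formula in step 1.

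| Share missed | Observed efficacy | Power, placebo 50% | Power, placebo 60% |
|---|---|---|---|
| none | 70% | 0.816 | 0.919 |
| 5% in both arms | 70% | 0.784 | 0.893 |
| 10% in both arms | 70% | 0.749 | 0.863 |
| 20% in both arms | 70% | 0.674 | 0.791 |
| 5% in placebo only | 68.4% | 0.761 | 0.875 |
| 10% in placebo only | 66.7% | 0.698 | 0.819 |
| 20% in placebo only | 62.5% | 0.556 | 0.674 |

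**4. The same in subjects.** Take 25 per arm, with 14 placebo and 4 active cases (assumed). Efficacy = 1 − active/placebo; p is two-sided Fisher.

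| Placebo v active cases | Efficacy | p |
|---|---|---|
| 14 v 4 | 71% | 0.007 |
| 13 v 4 | 69% | 0.016 |
| 12 v 4 | 67% | 0.032 |
| 11 v 4 | 64% | 0.062 |
| 10 v 4 | 60% | 0.114 |
| 12 v 3 | 75% | 0.012 |
| 11 v 3 | 73% | 0.026 |
| 10 v 3 | 70% | 0.051 |

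Significance is lost if three or four of 14 placebo cases (21–29%) and no active case are missed, or if four placebo cases and one active case are missed.

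**5. Where rescue would fall.** If rescue is proportional to illness and all active arms have 70% efficacy, placebo holds 1/(1 + 3 × 0.3) = 53% of rescued subjects across four arms. Using the previous challenge study's rates in section 1.0 (57.1%, 45.8% and 4.5%), with the 15 μg two-dose arm assumed between 4.5% and 45.8%, the share is 57.1/111.9 = 51% down to 57.1/153.2 = 37%.

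**6. Shedding.** Sampling runs over Days 3–9 and scheduled oseltamivir starts on the Day 8 morning, so the Day 9 sample is on treatment in every arm. The Day 8 wash follows the morning examination (7.1.13) but is not ordered against the first dose. Samples after early oseltamivir are on treatment only in the subjects who met a criterion, so their number may differ by arm. Paracetamol is not an antiviral and has no part in this.

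**The case against.** The strongest reply is that the escape pattern is an edge case. Diary cards are completed twice daily and cover the time since the last card, and a just-noticeable trace on an adjacent day is enough to count. Two or three simultaneous grade 2 symptoms with nothing on either side should be uncommon, and paracetamol is given only on request. This stands, and it limits the size of the problem; the rules still disagree.

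A second reply is that rescue handling belongs in the statistical analysis plan, which is not shown. That is fair for sensitivity analyses in general. Here, however, the protocol itself fixes the rescue triggers, the illness definitions and the shedding measure, and they do not fit together.

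A third is that shedding is a secondary analysis, and that section 5.2 expects the inpatient stay to outlast typical shedding even untreated. This makes the late on-treatment samples a minor matter and leaves early oseltamivir as the main issue.

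A reader might go further and infer that rescued cases are lost mostly from the placebo arm, so that efficacy is understated. The documents do not support that. They give no rescue use by arm, and the proportional calculation puts placebo at about 37–53% of the total. Equal proportional loss leaves efficacy unchanged: 10 v 3 still gives 70%.

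**Conclusion.** The concern holds in a limited form. Symptom-only rescue at grade 2 can begin before the two-day rule is met. A subject with the 0, 2, 0 pattern and no other qualifying finding is then scored as not ill, even if treatment caused the resolution. The temperature and listed grade 3 criteria are unaffected.

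The size depends on an unknown share of missed cases. An equal share across arms costs power only. Bias toward no effect needs a larger share of placebo cases to be missed, which is plausible but not shown. The larger losses shown, such as 14 v 4 falling to 10 v 4, are illustrations under assumed counts. The AUC mixes treated and untreated samples: by design and in all arms from Day 8, and possibly differentially after early oseltamivir. The trial is phase II and any bias of this kind would be conservative, but the repair is cheap and should be settled before unblinding.

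**What to change.** Leave the clinical rules untouched and reconcile 7.1.13 with 9.3.

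- **9.3.5:** state, before unblinding, that a subject given paracetamol or oseltamivir before Challenge Phase Day 8 under a symptom-only criterion counts as having illness. Exclude the scheduled Day 8 oseltamivir explicitly; otherwise its use in all subjects would turn isolated one-day grade 2 symptoms into illness and undo the two-day rule. Report results with and without this rule. Keep the infection requirement in 9.3.7.
- **9.3.8.2:** end the AUC at the Day 8 sample, and state that this sample is taken before that morning's first scheduled dose. For early starters, add a sensitivity analysis using only samples before the first antiviral dose. Carrying the last pre-treatment titer forward is not advised, because a near-peak value would inflate the AUC.
- **Case report form:** record the date and time of rescue doses. Section 7.3.5 requires new medications to be recorded but does not mention times.

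The cost is a few sentences and one data field. The downsides are that a few subjects with a single symptomatic day count as ill, that a treatment given on request becomes part of the definition (hence reporting both ways), and that the Day 9 sample leaves the AUC.

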On the morning of the second full challenge phase day (challenge phase day 2; day 41 ± 3 after first immunization), all remaining eligible and consenting subjects will receive a dose of viable, egg-grown A/Panama/2007/99 by intranasal drops. The challenge inoculum will be selected so as to achieve illness and infection rates of 50 - 70% in the subjects who received placebo during the immunization phase.

Between challenge phase day 2 (p.m.) and challenge phase day 9 (p.m.), subjects will complete a standard diary card of symptoms of influenza twice each day. During these days, oral temperatures will be measured at least four (4) times daily, and contents of the diary cards will be elicited by a directed interview and recorded, approximately every twelve (12) hours. Once per day, at approximately 24 hour intervals, each subject will have a directed physical examination of the ears, nose, throat, and chest. Once per day, and at approximately 24 hour intervals, each subject will have a nasal wash **and throat swab for detection and / or quantitation of influenza virus using culture, antigen detection or molecular biology techniques.** Tissue counts and weights will be collected throughout challenge as a surrogate of disease severity. Beginning on the morning of challenge phase day 8, each subject will begin five (5) days of twice-a-day treatment with oseltamivir to ensure termination of virus shedding. Amantidine will be available as an alternative treatment should intolerance to oseltamivir be a problem for any subject. Subjects will be re-evaluated in the p.m. hours of challenge phase day 9, and, if illness has resolved, be discharged. Any subject who is either febrile (oral temperature ≥ 37.9º C) or has persistent symptoms of grade 2 or greater will be retained in the facility for an additional 24 hours. Subjects remaining symptomatic will be referred for appropriate medical care. (Illness following inpatient influenza challenge is typically somewhat milder than community- acquired influenza, and short lived. This inpatient period, even without antiviral treatment, extends beyond the typical duration of virus shedding in this model.)

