## 7.4 Early Discontinuation:

Every reasonable effort should be made to ensure that each subject complies with the protocol and completes all study visits. However, a subject may withdraw or be withdrawn from participation if:

 The subject withdraws consent,

- The investigator recommends discontinuation in the interest of the subject’s safety or because of significant and irremediable protocol non-compliance,

 ID Biomedical, the ethics committee, or the MCA terminates the clinical trial.

Subjects must be stringently counseled that early withdrawal from the challenge isolation portion of the trial will be strongly discouraged, as it poses a risk both to the subject and to his/her contacts. Any subject insisting on early withdrawal during challenge isolation will be started immediately on a five (5) day course of oseltamivir (or amantidine), and will be encouraged to remain in the isolation unit as long as possible.

A complete Challenge Phase Day 20 – 30 (Final Follow-up Visit) evaluation and Study Termination case report form should be completed on any subject prematurely withdrawn from the clinical trial. No subject prematurely withdrawing/withdrawn will be replaced.

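### The amantadine alternative has conflicting durations in Sections 7.1.13, 7.1.14 and 7.4, and Section 7.1.13 does not say how the Day 8 oseltamivir course applies to subjects who started early

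*Protocol*

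**What the plan says.** Section 5.2 sets out the antiviral plan. From the morning of Challenge Phase Day 8, "each subject will begin five (5) days of twice-a-day treatment with oseltamivir to ensure termination of virus shedding". For those who cannot take it, "Amantidine will be available as an alternative treatment should intolerance to oseltamivir be a problem for any subject". Section 5.2 gives no separate length for amantadine.

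Section 7.1.13 repeats the rule: "On the MORNING of Challenge Phase Day 8, all subjects will initiate treatment with oseltamivir (75 mg orally), to be administered twice daily", for five days. For oseltamivir-intolerant subjects it substitutes "amantidine hydrochloride 200 mg orally once a day for three days or until influenza symptoms resolve". The bullet just before allows oseltamivir to start earlier than Day 8 when listed fever or symptom criteria are met, and states no course length.

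Section 7.1.14 (Day 9 p.m., the planned discharge) says that either drug continues as set out in 7.1.13. It then has subjects supplied with enough oseltamivir or amantadine "to complete their five-day regimen, and reminded to do so".

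Section 7.4 covers a subject who insists on leaving isolation early. Such a subject "will be started immediately on a five (5) day course of oseltamivir (or amantidine").

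Appendix B, Table B.2 marks oseltamivir on Challenge Phase Days 8 to 12 and has no row for amantadine.

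**The concern.** A single alternative treatment appears with two lengths. The section governing take-home supply points to the three-day or symptom-based rule and then calls the course five days. Whoever dispenses amantadine on Day 9 cannot satisfy both.

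The symptom clause also sits awkwardly with the purpose given in Section 5.2, which is to end shedding. The Day 8 treatment is given whether or not a subject is ill, so an end point defined by symptoms says nothing for a subject who has none.

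The discharge criteria in 7.1.14 are temperature, symptoms and physical findings. No negative virus test is required, so the remaining antiviral course is the measure against shedding that continues after discharge. If its length is unclear, subjects may leave with different supplies, and compliance or a deviation cannot be judged against one rule.

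A smaller gap concerns early oseltamivir. The text does not say whether a subject already on treatment finishes the course begun earlier or takes a further five days from Day 8.

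**Working it through.** No power or sample-size figure is involved. The check is a day count: last treatment day = start day + number of days − 1, in Challenge Phase days.

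**The plan's own figure.** Oseltamivir from Day 8 for five days (7.1.13): 8 + 5 − 1 = Day 12. This matches the five marks, Days 8 to 12, in Table B.2. For the standard course, Sections 5.2, 7.1.13, 7.1.14 and Table B.2 agree.

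**Amantadine.** Inputs: three days (7.1.13); five days (7.1.14 and, for early withdrawal, 7.4); planned discharge on Day 9 p.m.

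| Amantadine starts | Three days end | Five days counted from Day 8 end | Difference |
|---|---|---|---|
| Day 8 | 8 + 3 − 1 = Day 10 | Day 12 | 2 days |
| Day 9 | 9 + 3 − 1 = Day 11 | Day 12 | 1 day |
| Day 10 | 10 + 3 − 1 = Day 12 | Day 12 | none |

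The third column reads the five-day regimen of 7.1.14 as total antiviral cover from Day 8, which is the reading most favourable to the plan. Even so, three days of amantadine complete the five only with a switch on Day 10, after planned discharge. A switch on Day 9 gives one day of oseltamivir plus three of amantadine, a total of 1 + 3 = 4 days.

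**The symptom clause.** It supports at least two readings: stop at three days or at symptom resolution, whichever is earlier; or give three days and extend until symptoms resolve. The protocol does not choose. On either reading, symptom resolution supplies no end day for a subject without symptoms.

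**Early oseltamivir.** Let s be the start day, from 2 (after inoculation) to 7.

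- Five days from the actual start end on Day s + 4, that is Day 6 (s = 2) to Day 11 (s = 7). With s of 5 or less, the course is complete by Day 9 and there is nothing to take home.
- If the Day 8 course is also given and treatment is uninterrupted, it runs to Day 12, for 12 − s + 1 = 13 − s days: 11 days (s = 2) down to 6 days (s = 7).
- Example, s = 4: the course ends on Day 8 after five days, or on Day 12 after nine.

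The document does not state which applies.

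**Reach.** The last nasal wash and throat swab are on Day 9 (Section 7.2.7 and Table B.2). The three-day and five-day amantadine courses above part only after that day.

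**The case against.** The strongest reply is that little depends on this. Section 5.2 says the inpatient period outlasts the usual length of shedding in this model even without antivirals. Discharge also requires no fever, no grade 2 symptoms and no ominous findings, with a further 24 hours of retention as the default otherwise. The main oseltamivir course is stated consistently. All of this stands and limits the severity. It does not remove the contradiction on amantadine.

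The Section 7.4 course belongs to a different situation, early withdrawal, so it is weaker evidence of conflict than 7.1.14. That is also right; the conflict between 7.1.13 and 7.1.14 stands without it.

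Several stronger readings are tempting and are not supported:

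- A reader might infer that the Day 8 rule contradicts the early-start rule, so that early starters would be treated twice. The early-start bullet directly precedes the Day 8 bullet and can naturally be read as an exception; a subject already on oseltamivir does not initiate it. What remains is an unstated duration.
- A reader might infer that a symptom-free subject on amantadine would stop at once, so the course is three days at most. That is only one reading of an ambiguous clause.
- A reader might size the problem from the illness rate planned for placebo recipients. Illness in Section 9.3.5 is a threshold, so failing to meet it does not mean having no symptoms. The amantadine clause also applies only to oseltamivir-intolerant subjects, whose number is not given.
- A reader might carry the warning in Section 7.4 about risk to contacts over to the planned Day 9 discharge. That warning concerns early withdrawal from isolation.

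**Conclusion.** The concern holds as a minor internal inconsistency. Sections 7.1.13 and 7.1.14 give different lengths for the amantadine alternative, and 7.4 sides with five days in its own setting. For a switch on Day 8 or 9 the difference is two days or one day, counting the five-day regimen from Day 8. The symptom clause adds an ambiguity that the stated purpose does not settle. The early-start point is a gap in the text, with possible total courses of five days or, on the most literal reading, 6 to 11 days.

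Only oseltamivir-intolerant subjects and early starters are affected. The protocol gives the number of neither; the intolerant group is assumed to be small. The day counts assume uninterrupted treatment and the nominal schedule. The length of amantadine after discharge touches no virology endpoint, and nothing here bears on sample size or on the efficacy comparison. The practical effect is on what is dispensed at a discharge that requires no negative virus test, and on whether compliance can be judged against one rule.

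**What to change.** Reconcile Sections 5.2, 7.1.13, 7.1.14 and 7.4 so that each antiviral has one stated course, including how days already taken on the other drug count after a switch. If a symptom-based end is kept, word it so that it has a single meaning and covers subjects without symptoms. State in 7.1.13 how the Day 8 instruction applies to subjects who began oseltamivir earlier. Make the take-home supply in 7.1.14 follow from those statements, and show the alternative in Table B.2. The sponsor and medical investigator decide which course applies; this point asks only that the passages agree.

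The cost is wording in those sections, the table and the dispensing instruction. Design, sample size and analysis are unchanged.
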